#### Study population and recruitment

600 adults aged 18+ years will be recruited. Recruitment will occur in the greater Adelaide region (South Australia) via advertisements in social media and similar platforms. A passive snowballing technique will be used, recruited study participants would be asked to discuss the research project with their family, friends, peers and colleagues and this process will continue until the desired sample size is achieved. The patient interview, clinical and oral assessment, and dental plaque sampling will take place in dental clinics, Adelaide Dental School, University of Adelaide. The recruitment process will begin on June 2021.

#### Inclusion and exclusion criteria

Systemically and orally healthy adult’s ≥ 18 years of age would be selected. The inclusion criteria are: (1) presence of all set of teeth with the exception of impacted/missing wisdom teeth or orthodontic extraction; (2) periodontally healthy participants having probing depth (PD) of ≤ 4 mm and no loss of clinical attachment; (3) presence of less than 20% of bleeding on probing (BOP); (4) score of 2 or below in the Caries Assessment Spectrum and Treatment (CAST) index [38].

The exclusion criteria includes: (1) participants with any systemic disease such as diabetes, cardiovascular condition (angina or heart failure), cancer, respiratory disorder, bone or joint disorder, epilepsy, gastro-intestinal disorder (ulcerative colitis or Crohn’s disease) or kidney dysfunction; (2) pregnant or lactating mothers; (3) taking medication orally that may impact the oral microbiome in the last 3 months such as (i) antibiotics, anti-fungal, anti-viral, or anti-parasitic; (ii) corticosteroids (Prednisolone, Flonase, dexamethasone, Flovent); (iii) cytokines or drugs that can stimulate the immune system; (iv) methotrexate or other agents that can supress the immune system; (v) commercial probiotics (e.g. probiotic tablets or Yakult); (4) those who have undergone dental treatment (scaling or dental filling) in the last 3 months. Any persons who have ever tested positive for SARS-CoV-2 (COVID-19) or are having any flu like symptoms like fever, cough, shortness of breath or a recent travel history interstate or internationally would additionally be excluded.

#### Data collection

In view of the COVID-19 pandemic, strict sterilization and personal protection measures will be taken while clinically examining the participant and plaque/saliva sampling to reduce exposure to body. All research staff would wear personal protective equipment including masks and non-latex sterile gloves while conducting oral examinations.

Questionnaire: Data will be collected using a two self-report questionnaire. The questionnaire will be offered in both paper and online formats, depending upon participant preference. A pretested custom questionnaire has been formed by the authors to capture the socio-demographic data using the REDCap® (Research Electronic Data Capture) software [39]. The questionnaire will collect information on demographics, details on smoking and alcohol consumption, general health status, physical activity, oral health behaviour and emotional well-being (S3 File). The second questionnaire, the Dietary Questionnaire for Epidemiological Studies Version 3.2 (DQES v3.2) by the Cancer Council Victoria will be used to measure diet and nutritional habits [40].Anthropometric measurements: The height and weight of the participants will be taken and body mass index would be calculated.Clinical oral examination: The oral assessment will be done with study participant laying in a supine position whilst a registered dental clinician examines the hard and soft tissues of their mouth. BOP will be recorded as the overall percentage of sites with bleeding occurring within 15 seconds of probing. PD will be measured from the free gingival margin to the base of the pocket at the selected sites using a UNC-15 periodontal probe (Hu Friedy, Chicago, IL, USA).For caries assessment, the CAST index will be used. After removing excess saliva with cotton rolls or gauze, the entire dentition would be examined with a mouth mirror and probe and a score from 0–9 will be given. Participants with code 0 (No visible evidence of a distinct carious lesion), 1 (Pits and/or fissure are at least partially covered with a sealant material), and 2 (A cavity is restored with an (in) direct restorative material) will be considered as “healthy participants”, and a higher score would not be accepted.Dental plaque collection: On the day sample collection, the participants would be advised to abstain from brushing their teeth and using any form of mouthwash. Supragingival plaque samples would be collected from four sites (buccal surface of maxillary central incisor and lingual surface of mandibular central incisor and mesio-buccal surface of maxillary molar and mesio-buccal surface of mandibular molar) using sterile dental curette. The pooled plaque sample would be vortexed in 200μL of phosphate buffer solution and then samples would then be immediately transported to the Oral Microbiology Laboratory for inoculation in to the flow cells.Stimulated whole saliva collection: The collection would be conducted according to a method previously described [41]. The participant would be instructed to sit upright motionless and instructed to chew an inert gum. The participant would be asked to spit everything into the graduated collection tube. The fist two minute collection would be discarded, and then the next five minute collection would be retained for further analysis. A salivary flow rate would be caluclated based on the flow rate per min.

Additonally, the pH of the saliva will be determined using a saliva titration system. The level of acid produced will be assessed by flowing the saliva sample by adding 8ml of 10% glucose and incubating for 2 hours. A pH of 6.8 will be maintained by the titration of 0.1M NaOH.

#### Splitting of samples

The pooled plaque samples would be vortexed for 30s at low speed in 200 μl of phosphate buffer solution (PBS) for homogenization. A part of the sample (100μl) will be stored at -80°C and processed later for DNA extraction and high throughput sequencing and the second part (100μl) would be used for inoculation in the flow cell.

### Step 2: Inoculation and growth of the *in vitro* biofilm

The sample (100 μl) would be mixed with 1 ml of 25% modified version of Artificial Salivary Medium (ASM) before inoculation in the flow cell (Fig 2). The ASM includes the following components: 0.50 g/L tryptone (Oxoid, Hampshire, England), 0.50 g/L neutralised bacteriological peptone (Oxoid), 0.625 g/L type III porcine gastric mucin (Sigma-Aldrich, Steinheim, Germany), 0.25 g/L yeast extract (Oxoid), 0.05 g/L KCl, 0.05 g/L CaCl2, 0.088 g/L NaCl, and 1mg/L haemin (Sigma-Aldrich). The solution was supplemented with 2.5mM DTT (Sigma-Aldrich) and the pH was adjusted to 7.0 [42]. The sample would be injected into the inoculation port (Fig 2F) then be cultured on hydroxyapatite (HA) discs (Clarkson Chromatography Products Inc. PA, USA) in 3D-printed flow cells for a period of 14 days. The flow cell would remain static for 12h to ensure each HA discs would be coated with ASM, as this would facilitate the formation of acquired pellicle for bacterial adhesion. Based on our unpublished preliminary data, each flow cell will produce 16 discs with ~1.15x10^4^ live cells on each. After 14 days, the flow cell would be dissembled and all the 16 discs would be extracted. Half of the discs would be used for microscopic examination and the other half would be stored at -80° C until used for amplicon and shotgun sequencing.

**Fig 2 pone.0260433.g002:**
[figure not shown]
The flow cell and its components: The components of the system included; A medium reservoir (A), a multi-channel peristaltic pump (B), a break line (C), the flow cell (D), a slide heating tray (E), inoculation port (F), expelled into waste container (G).

#### Microscopic examination

Confocal Laser Scanning Microscopy (CLSM) and Scanning Electronic Microscopy (SEM) will be used to visualise the microbial communities grown on the eight HA discs. Microscopic examination is essential to ensure that biofilms are actively growing. CLSM semi-quantitatively analyses the proportion of living:dead microbes using BacLight® LIVE/DEAD staining and imaging using IMARIS® software [43]. SEM will determine the morphological structure of the biofilm.

#### DNA extraction and sequencing

DNA from all samples (PBS plaque sample and eight discs) and negative controls will be extracted using a DNeasy PowerSoil Pro Kit®. Amplicon and Shotgun will be employed to: (1) study the overall bacterial population structure and compare communities to existing data sets on healthy individuals (amplicon) and (2) identify specific species and characterize their functions (shotgun).

Amplicon Library analysis: Amplicon sequencing will be done by amplifying the 16S rRNA encoding the V_4_ gene region with region-specific primers, as previously described [44]. Amplicon libraries will then be cleaned, quantified, pooled, and custom sequenced in parallel to a level of >10, 000 sequences per sample on an Illumina MiSeq [44, 45]. The QIIME2 software will be used for analysis of all amplicon data [46]. In QIIME2, amplicon sequence variants (ASVs) will be taxonomically identified by comparisons to eHOMD and the SILVA databases. Alpha diversity (observed species and Shannon’s Diversity Index) and beta-diversity (unweighted UniFrac and Bray-Curtis indices) will be analysed. The donor microbiome will also be compared to healthy supragingival plaque specimens publicly available on QIITA, which is a web-based microbiome comparison platform that allows users to rapidly compare their data with Human Microbiome Project (HMP) and other submitted data sets [47].

Shotgun DNA sequencing library analysis: Shotgun sequencing is random sequencing across entire genomes [48]. To prepare shotgun libraries, custom DNA adaptors with sample specific barcodes will be ligated to random DNA fragments within the samples, as previously described [45]. After cleaning and pooling, shotgun libraries will be sequenced to at least 100 million sequences per sample on an Illumina NovaSeq. To identify bacterial species and functions in the shotgun data, we will map and remove all human sequences and then compare the remaining sequences to a custom curated RefSeq and HOMD genome database and KEGG protein predictions in two analytical pipelines: (1) the MetaPhylan and HUMAnN (2) and the MALT and MEGAN6 CE analysis pipeline packages [45]. This will enable the team to examine links between species and their functions. Bacterial genome assembly using GroopM will be done to link functions to certain species [49].

### Aim 2: Develop a delivery system for OMT therapy

To develop hydrogels as an OMT delivery vehicle, hydrogels comprising of dopamine and oxidized sodium alginate will be prepared in a multi-step process. First, sodium alginate will be oxidized by sodium periodate in an ethanol-water (1:1 v/v) mixture. Dopamine (DA) will then be grafted to the oxidized sodium alginate following a well-established bioconjugation method. Specifically, the amine group of the dopamine will be conjugated to the carboxylic acid group of oxidized sodium alginate using EDC (1-(3-(Dimethylamino) propyl)-3-ethylcarbodiimide hydrochloride) and NHS (*N*-hydroxysuccinimide) as a coupling agent. The product will be purified by extensive dialysis and used for the hydrogel preparation.

For the hydrogel preparation, dopamine grafted oxidized sodium alginate will be first mixed with acrylamide (AM) followed by the addition of ammonium persulfate (APS), *N*,*N*′-methylenebisacrylamide (BIS), and *N*,*N*,*N*′,*N*′ tetramethylethylenediamine in an inert (N_2_) atmosphere. Inert atmosphere is necessary to prevent the over oxidation of dopamine. A transparent hydrogel will be formed after 4 hours. The composition of the hydrogel can be varied by changing the amount of dopamine grafted oxidized sodium alginate in the final solution.

In addition, hydrogel containing polydopamine (PDA) and polyacrylamide (PAM) will also be prepared as an alternative. In such case, dopamine will be polymerized first in the presence of sodium hydroxide followed by the sequential addition of AM, APS, and BIS under mechanical stirring in an ice bath. PDA-PAM single network hydrogel will be formed after 10 min. DA/AM ratio will be varied to optimize the properties of the hydrogels.

Hydrogel mechanical stability will be assessed by determining their storage modulus (G’) and the loss tangent (ratio of loss modulus G” to storage modulus G’). The chemical characterization of the hydrogel will be assessed by FT-IR spectroscopy, XPS, and thermo gravimetric analysis. The morphological characterization of the hydrogel will be performed by SEM and atomic force microscopy (AFM). After successful characterization, microbes will be added into the hydrogel, and their survival monitored using microscopy and sequenced (as described above) by every 12 hours for a three-day period, reminiscent of the transport and application time needed for OMT therapy [50]. However, the efficacy of this application method still needs to be examined in murine models, and if we experience unforeseen issues with the hydrogel approach, other strategies will be explored, such as application of plaque microbiota in buffers (e.g., as the canine OMT study was done), varnishes, or mouthwashes.

### Aim 3: To test the oral microbiome transplant in rodent models

#### Ethics

Before the start of the study, ethical approval will be obtained from the University of Adelaide Animal Ethics Committee and comply with National Health and Research Council (Australia) Code of Practice for Animal Care in Research and Training (M-2021-022).

#### Animals

6–8 weeks old, Sprague-Dawley rats and Balb/c mice will be used in healthy trials of OMT. The animals will be obtained from the Laboratory Animal Services of the University of Adelaide and will be housed in animal holding facilities. All animals will be subjected to 5 days of acclimatization and be housed together to promote amelioration of the microbiota between animals. Animals would be caged in screen-bottomed cages, as this prevents accumulation of faeces and urine in the cage. Bedding for the animals will not be used as the animals might ingest it, which can lead to impaction in fissures and interproximal areas [51]. The animals’ diet will comprise powdered, sterile, non-granular food to prevent impaction of food around the gingiva and they would have access to sterile non-acidic water *ad libitum*. They will be kept in a room with a 12-hr light/dark cycle with temperature ranging from 22 to 24°C [52].

### Aim 3a) Examine the safety and efficacy of OMT of human microbiome in healthy mouse/rats

#### Experimental design

Two groups per experiment will be repeated with six different donor microbiotas:

*Control group 1*: Placement of hydrogel (without bacteria) once daily for three days on tongue, buccal areas, gingiva, palate, and tooth surfaces.*Experimental group 1*: OMT (donor microbiota in hydrogel) once daily for three days, as above.

Microbiota assessments will be made at baseline, 1 day after the final OMT treatment, and 4-weeks post-OMT, using microscopy and DNA sequencing, as described above. A behavioural and physical health check of the animals will be done weekly and at the end of the study. The animals would be replaced if there were any deviation from normal healthy behaviour. To collect microbiota during the experiment, the oral cavity of an anesthetized mouth will be swabbed for 30 sec using nylon swabs, over the tongue, buccal areas, gingiva, palate, and tooth surfaces. Swabs will be placed into sterile PBS buffer, alongside a negative control, and analysed immediately or frozen at -80C until DNA extraction. At the end, rodents will be swabbed a final time, and concluding oral samples taken for microscopy and DNA analysis.

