
## Study aims

The specific aims of the study are as follows:

Aim 1: Describing and identifying the healthy donor and testing the oral biofilm growth using a novel *in vitro* flow cell model.Aim 2: Develop a delivery system for OMT therapy, including hydrogel applications:Aim 3: Test oral microbiota transplant in rodent models:
Examine the safety and efficacy of OMT of human microbiota in healthy rodents.Examine the safety and efficacy of OMT in a rodent caries and periodontal disease model.

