#### Periodontitis model

Experimental periodontitis will be induced in 5–7 week old BALB/c mice after an initial 5 days being fed with either control or experimental diet and receiving kanamycin (1mg/mL) ad libitum for a 7-day period in their drinking water to supress the indigenous oral microbiota [56]. For induction of experimental periodontitis, the mice will be inoculated with either the suspension vehicle only (2% carboxyl-methylcellulose) or *Fusobacterium nucleatum* and *Porphyromonas gingivalis* in the periodontium for 5 weeks twice weekly. The inoculation will consist of 100 μL of bacteria either 10^10^ colony‐forming units/mL of *P*. *gingivalis* alone or 5×10^9^ colony‐forming units/mL of *P*.*gingivalis* and 5×10^9^ colony‐forming units/mL of *F*.*nucleatum* suspended in 2% carboxymethyl cellulose [57]. Experimental mice will receive the OMT one week after *F*.*nucleatum* and *P*.*gingivalis* inoculation. Each group will consist of eight mice from different litters:

*Control group 1*: orally inoculated with the suspension vehicle.*Control group 2*: mice inoculated with *F*.*nucleatum* and *P*.*gingivalis*.*Experimental group 1*: Inoculated with suspension vehicle with OMT once daily for 3 days.*Experimental group 2*: *F*.*nucleatum* and *P*.*gingivalis* inoculation followed by OMT once daily for 3 days.

To reduce the effect of periodontal inflammation all the mice would undergo full mouth scaling and polishing before oral microbiome transplantation on experimental group. To further supress the resident microbiota of the recipient mice, subgingival and oral irrigation with 0.1% sodium hypochlorite would be done for 5 min. The sodium hypochlorite would then be inactivated by using 23μM buffered sodium ascorbate for 10 min [25, 27]. The OMT would be delivered locally in hydrogel loaded dental tray. The loss of alveolar bone will be measured prior to OMTs/infections and throughout the experiment by live animal computed tomography scanner (Skyscan 1076 High Resolution *In Vivo* Scanner; Skyscan, Kontich, Belgium) measuring changes in bone volume from the cemento-enamel junction to the alveolar bone crest in the jaws [58]. The scanner has a 10 megapixel camera with a tungsten 100 kV X-ray source and a spot size of 5 um. For scanning, the X-ray source will be operated at 75 kV X-ray source and 120 mA with a 1-mm tungsten filter. The scanning width would be set to 35 mm with a pixel of 9 um pixels [58].

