After 5 weeks, the rats will be humanely euthanized by CO_2_ and the jaws would be dissected to similar procedure described as above for caries model. Alveolar bone loss will be assessed using a Leica MZI6FA stereomicroscope (Leica Microsystems, Wetzlar, Germany) compared to controls [57]. Microbiome will be assessed by microscopy and high-throughput DNA sequencing.

All the data will be compared using ANOVA, and experiments will consist of three biological replicates. For safety of OMT, the presence and absence of discomfort would be measured by monitoring the vital parameters and any adverse reactions of the oral mucosa like redness, inflammation, bleeding, friability of the tissues to the transplants would be recorded separately.

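### Aim 3a replaces animals whose behaviour deviates from normal, with no limit to the period before dosing and no statement that replaced animals stay in the safety count

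*Protocol article*

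**What the plan says.** The Study aims section gives the purpose of this experiment: "Examine the safety and efficacy of OMT of human microbiota in healthy rodents". Aim 3a, Experimental design, sets a blank-hydrogel control against OMT in hydrogel, each applied daily for three days: "Two groups per experiment will be repeated with six different donor microbiotas". It gives no number of animals per group. On follow-up it says: "Microbiota assessments will be made at baseline, 1 day after the final OMT treatment, and 4-weeks post-OMT".

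On health monitoring in Aim 3a: "A behavioural and physical health check of the animals will be done weekly and at the end of the study". The sentence straight after it is the replacement rule: "The animals would be replaced if there were any deviation from normal healthy behaviour".

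The only text introduced as a safety measure stands in the closing paragraphs of Aim 3b, after the periodontitis model: "For safety of OMT, the presence and absence of discomfort would be measured by monitoring the vital parameters and any adverse reactions of the oral". The quote breaks off where the text turns to reactions of the mucosa, which are to be noted separately. The same paragraph gives the analysis: "All the data will be compared using ANOVA, and experiments will consist of three biological replicates". Neither sentence says how a replaced animal is handled.

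**The concern.** In a healthy animal, a change in behaviour after the transplant is one of the ways harm would show itself. Aim 3a makes that change the reason for putting another animal in the first one's place. If the groups as finally completed are analysed, they have been selected on something that happened after treatment and may have been caused by it. The selection acts in both arms, so the comparison with blank hydrogel can no longer show a difference on this outcome.

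The microbiota result is affected too. The 4-week assessment would describe animals that kept normal behaviour after OMT, mixed with replacements that started later. Whether the donor community establishes itself in animals that reacted to it would not be seen.

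The Background lists limited negative outcomes in a rodent model among the characteristics of a super donor, and says the study will supply foundational data on whether and how human trials should proceed. A safety result that leans towards no harm would carry into both uses.

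**Working it through.** The article states no group size, event rate or power for Aim 3a, so there is no figure to reproduce. The check has three parts.

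**1. Does the rule apply after dosing?** Inputs: acclimatisation of 5 days (Animals section); three days of application and follow-up to 4 weeks afterwards (Aim 3a); health checks weekly and at the end.

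- Length of the period: 5 + 3 + 28 = 36 days, if dosing follows acclimatisation directly.
- Checks seven days apart can fall at most once in a 5-day window. At most one weekly check therefore precedes the first application, and the others and the final check come after it.
- The replacement sentence names no period, no arm and no exception for causes related to treatment. As written, it operates mainly after dosing.

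**2. What do the completed groups show?** Let p be the true probability that a dosed animal shows a behavioural deviation, and n the group size.

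- Under the rule, each animal that deviates is replaced, and so is a replacement that deviates. The completed group has 0 deviations out of n for any p.
- This holds in both arms. With assumed rates of 30% on OMT and 5% on blank hydrogel, the true difference is 30 − 5 = 25 percentage points. The difference between completed groups is 0 − 0 = 0.
- The expected share of places held by a replacement at the end is np/n = p, so 5% to 30% over the range below. This is the part of the 4-week microbiota sample that comes from later starters.

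**3. How many events could be lost?** Both n and p are assumptions. The periodontitis model has 8 per group ("Each group will consist of eight mice from different litters"). The caries model spreads eight rats over four groups, which is 8/4 = 2 per group. Formulas: expected events = np; chance of at least one event = 1 − (1 − p)^n.

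| Assumed true rate p | Expected events, n = 8 | Chance of at least one, n = 8 | Chance of at least one, n = 2 |
|---|---|---|---|
| 5% | 0.4 | 1 − 0.95^8 = 34% | 1 − 0.95^2 = 10% |
| 10% | 0.8 | 1 − 0.90^8 = 57% | 1 − 0.90^2 = 19% |
| 20% | 1.6 | 1 − 0.80^8 = 83% | 1 − 0.80^2 = 36% |
| 30% | 2.4 | 1 − 0.70^8 = 94% | 1 − 0.70^2 = 51% |

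If the originally dosed animals stay in the denominator, these events are visible. If only the completed groups are analysed, none of them is.

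**The case against.** **Replacing an animal is not the same as deleting its data.** A reader might infer that the events are certainly discarded and that the completed group is healthy whatever the truth. The article does not say so. Loss of the events needs a further step, that only the completed groups are reported, and that step is unstated. The conclusion must therefore be conditional. The rule itself stands, because nothing in the text retains the first animal.

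**The protocol has another safety measure.** The recording of discomfort and mucosal reactions speaks of OMT safety in general and follows a sentence about all the data, so it can be read as covering Aim 3a. If it does, some events survive. It still closes Aim 3b, does not mention behavioural deviation or replaced animals, and leaves the rule in force. A reader might also take the weekly check to be the safety endpoint of Aim 3a; the article does not call it that.

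**The trigger is narrow.** The check is behavioural and physical, but replacement follows only a behavioural deviation. A reader might infer that every unwell animal is swapped. On the literal words, a mucosal or physical finding without a change in behaviour does not lead to replacement.

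**The article is condensed.** How withdrawn animals are counted may be left to the full animal protocol. That is fair, and a missing denominator rule alone would not be a finding. The open-ended replacement sentence is different, because it is stated outright and a fuller document would have to restrict it.

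**Conclusion.** The point holds in conditional form. The replacement rule is not limited to the time before dosing, and the article does not say that replaced animals remain in the safety count. If the completed groups are analysed, behavioural deviations after OMT disappear from both arms, safety is biased towards no harm, and the 4-week microbiota result is conditioned on animals that tolerated the transplant.

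The direction of the bias follows from the rule and does not depend on any assumed number. Its size is unknown. The 34% to 94% chance of at least one event per group is an illustration that borrows 8 per group from the periodontitis model and assumes true rates of 5% to 30%; at 2 per group the range is 10% to 51%.

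Two stronger readings are not supported. A reader might infer that Aim 3a is a formal gate to the disease models or to human trials. The article sets no go/no-go step between Aims 3a and 3b, and its Conclusion says that further safety and efficacy work must precede human trials. A reader might also pool the six donors and draw a tight upper confidence limit from a zero count. The article plans no such pooled report and no such limit.

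**What to change.** In Aim 3a, Experimental design, change the replacement sentence and add the counting rule:

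- Allow replacement only before the first application of hydrogel or OMT.
- From the first application on, keep every dosed animal in its group's safety denominator.
- Record each deviation or removal with its date, group and donor, and compare OMT with blank hydrogel on these counts.
- If animals are added later to complete the microbiota sample, report those results with and without them.
- State whether the recording of discomfort and mucosal reactions described at the end of Aim 3b also applies to Aim 3a.

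Removal of an animal for welfare reasons is unaffected; only the counting changes. The cost is a few sentences in the protocol, and some groups may have incomplete 4-week microbiota samples.
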